### Study outcomes

2.8

#### Primary outcome

2.8.1

The main efficacy outcome is a reduction in the mean level of plasma LDL-C at 3 months of 4.6 mg/dL (0.3 mmol/L) or more in the intervention diet group compared to the control diet group.

#### Secondary outcomes: all at 3 months

2.8.2

1)Levels of serum lipid profile: Significant reduction in the mean TC and triglycerides and significant increase in mean HDL-C in the intervention diet group compared to the control diet group.2)Improvements in the levels of serum inflammation markers vascular cell adhesion molecule, Intracellular Adhesion Molecule, Interleukin-6, apolipoprotein A and B in the intervention diet group compared to the control diet group.3)Safety: Frequency of AE and SAE by intervention group.4)Feasibility, adherence, and acceptability:a)the proportion of patients who complete the intervention at 3 months and time from symptom onset to intervention as a measure of feasibility;b)median MEDAS score at the end of the follow-up and adequacy of the interventions as assessed by the quantitative evaluation of the food questionnaires at 30, 60, and 90 days (percentage of adequacy) to measure adherence;c)acceptability will be assessed at 90 days using a structured questionnaire.

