MeDi improves lipid profile, insulin sensitivity, glycemic control and decreases blood pressure, and new-onset diabetes, all strong risk factors for stroke.^[17,18]^ Furthermore, there are several beneficial nutrients abundant in the MeDi that could act on inflammatory biomarkers such as adhesion molecules, cytokines, or molecules related to the stability of atherosclerotic plaque.^[19]^ On the other hand, Avocados, although not part of the classical MeDi, are another nutrient-dense source of MUFA, rich in vitamins, minerals, fiber, phytosterols, and polyphenols. A meta-analysis of randomized clinical trials showed that Avocado-substituted diets significantly decrease the levels of total cholesterol (TC), low-density lipoprotein cholesterol (LDL-C), and triglycerides.^[20]^ A comprehensive review on the effect of Avocados concluded that they can be used as dietary supplements for the treatment of different components of the metabolic syndrome.^[21]^ No evidence exists on the effect of Avocados on stroke prevention.

Lowering LDL-C levels prevent ischemic stroke recurrence in an inverse linear relationship, without a floor effect.^[22]^ Interventions to further decrease LDL-C levels show significantly lower recurrence rates of stroke.^[23–26]^

Our primary aim is to demonstrate a reduction in LDL-C in patients who had a recent (1 month) ischemic stroke receiving a MeDi based on Avocados compared to a low-fat high-complex carbohydrate diet after 3 months. Secondary aims include the safety and feasibility of the interventions.

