#### Secondary

1.1.2

1)To show an improvement in the serum lipid profile (reduction of TC and triglycerides; increase in high density lipoprotein cholesterol [HDL-C]) in patients with IS receiving the intervention diet compared to the control diet after 3 months.2)To investigate the change in serum inflammation markers in patients with IS receiving the intervention diet compared to the control diet after 3 months.3)To investigate safety of the intervention diet compared to the control diet after 3 months.4)To investigate feasibility, adherence, and acceptability of the intervention diet compared to the control diet after 3 months.

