### Measurements

2.10

Anthropometric measurements are performed by a study nurse or a study nutritionist according to the study schedule (Table 1). Weight and height are measured by using standard calibrated scales, respectively; waist circumference midway between the lowest rib and the iliac crest by using an anthropometric tape, and blood pressure after 10 minutes of rest in triplicate with a standard calibrated sphygmomanometer.

Blood samples are collected following overnight fasting for at least 10 ± 2 hours, at baseline and at 3 months, coded, centrifuged, and processed in the morning (lipids) at Clínica Alemana or stored at <80°C until assayed (for inflammatory biomarkers, see supplement) at The Medical Chemistry Center, Universidad del Desarrollo. Total cholesterol, LDL-C, HDL-C, and TG are processed with a homogeneous enzymatic colorimetric test in the chemistry automatic analyzer COBAS 8000 platform (Cobas, Roche Diagnostics) upon arrival to the laboratory. All tests are performed according to the manufacturer's instructions. The laboratory technicians are masked to the interventions. Analyses are performed for each participant in frozen samples of whole serum or plasma, as appropriate. Details of the analysis are provided in the Supplementary Material.

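### Apolipoproteins A and B are listed as serum inflammation markers, so a fall in apolipoprotein B that follows LDL-C could be reported as an improvement in inflammation

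*Protocol article*

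**What the plan says.** The protocol article keeps lipids and inflammation apart. Section 1.1.2 has one secondary objective on the lipid profile and a separate one on inflammation, worded "To investigate the change in serum inflammation markers in patients with IS receiving the intervention diet compared to the control diet after 3 months". That objective does not name the markers.

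Section 2.8.2 does. Its first item is "Levels of serum lipid profile: Significant reduction in the mean TC and triglycerides and significant increase in mean HDL-C", with no apolipoprotein in it. Its second item is "Improvements in the levels of serum inflammation markers vascular cell adhesion molecule, Intracellular Adhesion Molecule, Interleukin-6, apolipoprotein A and B", again comparing the intervention diet with the control diet.

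The Introduction, where it argues that a Mediterranean diet may act on inflammation, speaks of "inflammatory biomarkers such as adhesion molecules, cytokines, or molecules related to the stability of atherosclerotic plaque".

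The primary outcome in section 2.8.1 is LDL-C: "The main efficacy outcome is a reduction in the mean level of plasma LDL-C at 3 months of 4.6 mg/dL".

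Section 2.10 names the lipid panel, "Total cholesterol, LDL-C, HDL-C, and TG are processed with a homogeneous enzymatic colorimetric test", and covers the stored samples with the note "for inflammatory biomarkers, see supplement". That supplement is not among the documents at hand.

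**The concern.** Apolipoprotein B is the protein of LDL and related particles, and the apolipoprotein A usually measured alongside it belongs to HDL. Neither is a measure of inflammation in the sense in which an adhesion molecule or a cytokine is. Placing them in the inflammation outcome mixes two questions that the objectives separate: does the diet change lipids, and does it change inflammation?

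Apolipoprotein B matters most here because it is tied to the primary outcome. If the diet lowers LDL-C and does nothing else, apolipoprotein B would be expected to fall too. Under the present list, that fall is an improvement in a named inflammation marker, so the lipid result could reappear as evidence of a second, separate benefit.

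The Discussion describes this as a pilot intended to help design a phase 3 trial. A mislabelled inflammation signal could then influence the choice of outcomes or the rationale for that trial.

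**Working it through.** The article gives no figure on this point, so there is none to reproduce. The check compares what it says in different places.

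**Step 1: sort the five analytes.** The second column applies the Introduction's three kinds of marker (adhesion molecules, cytokines, plaque-stability molecules). The third gives the kind of molecule, which is general knowledge and not stated in the article.

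| Analyte in the inflammation outcome | Kind named in the Introduction | Kind of molecule |
|---|---|---|
| Vascular cell adhesion molecule (VCAM) | adhesion molecule | adhesion molecule |
| Intracellular Adhesion Molecule (ICAM) | adhesion molecule | adhesion molecule |
| Interleukin-6 (IL-6) | cytokine | cytokine |
| Apolipoprotein A | none | lipoprotein component |
| Apolipoprotein B | none | lipoprotein component, carried on LDL |

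Three of the five fit and two do not: 2/5 = 40%. Moving those two leaves 5 − 2 = 3 inflammation markers.

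**Step 2: look for another home or an explanation.** The lipid objective and the lipid outcome both contain total cholesterol, triglycerides and HDL-C only. The lipid panel in section 2.10 adds LDL-C. Nowhere in the article are the apolipoproteins placed with the lipids, and nowhere does it explain why they count as inflammation markers.

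**Step 3: compare the wording of the two outcomes.** The lipid outcome states a direction for each measure: down for total cholesterol and triglycerides, up for HDL-C. The inflammation outcome has only the general notion of improvement for all five. For the adhesion molecules and interleukin-6, improvement means lower. For apolipoprotein B it also means lower. For apolipoprotein A it depends on which protein is meant, which the article does not say; if it is the HDL protein, improvement would mean higher, in line with the aim for HDL-C.

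**Step 4: follow one scenario.** Suppose the diet lowers LDL-C, apolipoprotein B falls with it, and VCAM, ICAM and IL-6 are unchanged. The list in section 2.8.2 permits the statement that a serum inflammation marker improved. With the two apolipoproteins listed under lipids, the same data would permit only a statement about lipids.

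**The case against.** Four fair points can be made in favour of the plan.

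- **The analytes are named one by one.** There is no composite, no score and no rule that any one of five suffices. A reader who sees all five results would see that apolipoprotein B moved and interleukin-6 did not. This stands, and it limits the harm: the misreading is possible, not built in.
- **The inflammation objective is only to investigate a change.** It has no success criterion, unlike the lipid objective, which sets out to show an improvement. This also stands. A reader might infer that a fall in apolipoprotein B would cause the inflammation objective to be met, but the article sets no threshold for meeting it.
- **The Introduction's list is illustrative.** It is introduced as examples, so the absence of apolipoproteins does not amount to a contradiction within the article. This stands. The case rests on what apolipoproteins are, and the Introduction is only consistent with it.
- **Overlap with LDL-C is not new.** Total cholesterol includes LDL-C and is already a secondary outcome, and apolipoprotein B will remain correlated with LDL-C wherever it is listed. That is true, but total cholesterol is reported as a lipid. The fault here is the label, and the label decides which conclusion a result can support.

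The grouping may simply reflect which stored samples are assayed together, and the supplement might say so. A shared assay batch would explain the list but would not make the apolipoproteins inflammation markers. Details such as the direction for each marker may also sit in a supplement or analysis plan not at hand, so their absence alone is no fault. The classification itself, however, is stated in the outcome definition, and an analysis plan that follows it would carry it forward.

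**Conclusion.** The point holds in a limited form. Two of the five analytes in the inflammation outcome are lipoprotein components, and one of them is expected to follow the primary outcome. A fall in apolipoprotein B could therefore be reported as an improvement in an inflammation marker with inflammation unchanged.

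This rests on two pieces of general knowledge that the article does not state: that apolipoproteins are components of lipoproteins, and that apolipoprotein B tends to move with LDL-C. The first is a matter of definition and is enough to show the misclassification. The second is needed only for the consequence.

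A reader might go further and put a probability on a spurious inflammation finding, for instance by assuming how closely the apolipoprotein B effect matches the LDL-C effect. The article does not support such a figure. It gives no ratio of effects and no decision rule across the five markers, and the chance of detecting a real apolipoprotein B effect is not comparable with a false-positive rate for the other three. The size is therefore best given as a count: two of five markers in the wrong outcome, in one secondary outcome. The primary analysis and the sample size are not affected.

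**What to change.** Move apolipoproteins A and B from the second to the first item of section 2.8.2, and extend the lipid objective in section 1.1.2 to match. State which apolipoprotein A is meant and give the expected direction for each of the two, as is already done for the other lipids. Limit the second item, and any conclusion on inflammation, to VCAM, ICAM and IL-6, with improvement defined as a lower level.

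This is a change of wording. It needs no further patients, samples or assays, and the analysis of LDL-C stays as it is. The downside is that the inflammation conclusion rests on three markers instead of five.

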### Randomization

2.5

Eligible patients are randomly assigned in a 1:1 ratio by study personnel to either diet intervention, using a desktop minimization program (MinimPy 0.3, Python Software Foundation), balanced by sex, age group <70 and ≥70 years (this is the median age of patients admitted with stroke in Clínica Alemana), and previous adherence to a Mediterranean diet as defined according to the Mediterranean Diet Adherence Screener (MEDAS) score <7 or ≥7 (this is the median score found in stroke patients in our institutional registry) (Fig. 1).^[29,30]^

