### Intervention

2.7

We chose a MeDi based on Avocados because of the need to have stronger evidence to support current recommendations and because avocados are widely available and used in many parts of the world more so than olive oil. We chose the low-fat control diet because it is similar to what many clinicians and dietitians still recommend and what patients do to lower cholesterol levels after stroke. We improved it using high-quality complex carbohydrates (whole grains) and fiber content.

The elaboration of diets, the content of the sessions, and written material were made and reviewed by an experienced physician nutritionist specialist and a registered dietitian nutritionist (nutritionist) with experience in Mediterranean and low-fat high-complex diets. The study nutritionist and study nurses underwent initial specific training in all study procedures by the study investigators, and subsequently all study interventions are reviewed in weekly meetings.

As part of our institutional stroke registry in all patients, a MEDAS score is obtained, which is used for randomization. The randomized diet is notified by an investigator to the study nutritionist after consent is obtained. This study nutritionist is in charge and follows the patients throughout the study.

Anthropometric measurements are performed in person by a study nurse or study nutritionist according to the study schedule (Table 1).

**Table 1 T1:** Schedule of study evaluations.

Evaluation	Baseline	30 d	60 d	90 d
Eligibility	X			
Modified Rankin scale score	X			X
14 item Mediterranean diet questionnaire (MEDAS)	X			X
Written informed consent	X			
Randomization	X			
Secondary prevention medication questionnaire	X			X
Food frequency questionnaire	X			X
24-h food recall questionnaire		X	X	X
Rapid Assessment of Physical activity questionnaire (RAPA)	X			X
Anthropometric measures	X			X
Study blood samples	X			X
Allocated diet administration	X			
Nutritional counseling and dietary reinforcements	X	X	X	X
Questionnaire of AEs and SAEs		X	X	X
Telephone follow-up		X	X	
In person follow-up				X
Trial acceptability questionnaire				X

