Both diets include natural foods, little processed, and naturally low in sodium, and cooking with little added salt and using spices to season meals is reinforced during food education. With these guidelines, it is intended that the patient consumes a maximum of 5 g of salt per day between foods that contains it and the added salt. In both diets, the consumption of oil is daily, and it is recommended to include it raw to dress salads. The MUFA content of the low-fat high-quality carbohydrates is 12% to 14% versus 22% in the Mediterranean diet; therefore, the selection of foods that are included in these minutes corresponds to this calculation. The contribution of olive oil to be used is lower than that in the classical Mediterranean diet and can be replaced by canola oil if the patient does not consume olive oil, and the frequency of foods rich in MUFA (nuts, avocado) and PUFA (fish) is also less than that indicated in the Mediterranean diet. Both diets include complex carbohydrates, that is, from whole grains, fruits, vegetables, legumes, meats, and low-fat dairy products, and very low or no contribution of simple sugars. In patients with diabetes mellitus, the contribution of complex carbohydrates is the same as that in non-diabetic patients. Depending on the pharmacological treatment that the patient has for diabetes mellitus, an adjustment of the number of mealtimes can be made to avoid hypoglycemia if the patient uses sulfonylureas or insulin. The meal plan includes specific recommendations for each diet intervention, as well as a menu divided into 4 meals and a snack during the day with options for 14 days. This menu must be replicated and combined during the 3 months of patient participation.

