To maintain diet fidelity with the intervention, in all contacts the study nutritionist emphasizes that the portions and frequencies of food of the diet assigned to the patient are respected, solve specific doubts, and inquire about AE and SAE. The food surveys are analyzed qualitatively and quantitatively by the study nutritionist in charge of carrying them out. The qualitative analysis considers the number of meals per day, fluid intake, and quality of the food consumed, which is compared to each of the diet interventions. The quantitative analysis is carried out by obtaining the ingredients and quantities of each food preparation that the patient consumes, this is then transformed into portions to obtain the intake of calories, carbohydrates, fats, and proteins. This is compared with the requirements of the assigned diet and the % of adequacy is calculated ([intake value/requirement value] × 100). An adequate intake is considered if the macronutrient is in a percentage of adequacy of 90% to 110%. We use as a reference the contributions of nutrients and calories from the “Exchange portions and Chemical Composition of foods of the Chilean food pyramid” National Institute of Food Technologies, 1999 and its update “Food Composition Table” National Institute of Food Technologies, 2018.^[31]^ This information is used to personalize each interview and adjust counselling.

As part of the institutional protocol and Chilean stroke national guidelines, all patients receive appropriate secondary stroke prevention and are discharged with an antithrombotic statin at high doses (usually atorvastatin 80 mg day, a hypotensive, and if necessary, a hypoglycemic drug). The patients are counseled at each study visit to keep their secondary prevention medications according to their treating physician prescriptions.

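### The end-of-follow-up MEDAS score is listed as an adherence measure for both arms but cannot measure adherence to the control diet, and neither stated adherence measure is shown to capture avocado intake.

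*Protocol article*

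**What the plan says.** The fourth secondary objective (section 1.1.2) is comparative: "To investigate feasibility, adherence, and acceptability of the intervention diet compared to the control diet after 3 months". Section 2.8.2 gives two measures for its adherence part: "median MEDAS score at the end of the follow-up and adequacy of the interventions as assessed by the quantitative evaluation of the food questionnaires", with the questionnaires taken at 30, 60 and 90 days.

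On MEDAS, section 2.5 makes the purpose of the score clear, because minimization uses "previous adherence to a Mediterranean diet as defined according to the Mediterranean Diet Adherence Screener (MEDAS) score <7 or ≥7". It gives 7 as the median among stroke patients in the institutional registry. Table 1 schedules the "14 item Mediterranean diet questionnaire (MEDAS") at baseline and at 90 days.

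On adequacy, section 2.7 converts reported intake into calories, carbohydrates, fats and proteins. It continues: "This is compared with the requirements of the assigned diet and the % of adequacy is calculated". The rule for a patient is "An adequate intake is considered if the macronutrient is in a percentage of adequacy of 90% to 110" per cent.

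On the diets, section 2.7 says that the control diet uses less olive oil than the classical Mediterranean diet and that "the frequency of foods rich in MUFA (nuts, avocado) and PUFA (fish) is also less than that indicated in the Mediterranean diet". The Introduction says "Avocados, although not part of the classical MeDi, are another nutrient-dense source of MUFA".

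Section 2.17 plans a mixed model for percentage of adequacy, a sensitivity analysis of the efficacy findings by adherence, and a per-protocol analysis. It does not say which measure defines adherence in the last two.

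**The concern.** A score that rises with Mediterranean eating has a clear direction in the intervention arm. In the control arm it does not: a rise over follow-up may mean movement towards the other diet, and a low value may be what the control diet intends. A reader who takes two high final medians as good adherence in both arms could be looking at poor separation between the diets.

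The intervention arm has a separate gap. What distinguishes this diet is avocado, which the article places outside the classical Mediterranean pattern. If neither adherence measure registers avocado, a null LDL-C result cannot be traced to patients not eating it, and a positive result cannot be tied to it. Finally, the MEDAS outcome is stated as a final score only, so it mixes the effect of counselling with eating habits at entry.

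**Working it through.** The plan states no figure for this point, so there is none to reproduce. The check sets the passages side by side and then applies the adequacy rule to the two diets.

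**1. Direction of MEDAS.** Section 2.5 uses it as a measure of adherence to a Mediterranean diet. Section 2.7 makes the control diet lower in olive oil, nuts, avocado and fish. Section 2.8.2 nevertheless lists the final median as an adherence measure without naming an arm. A higher score is therefore not evidence of better control-diet adherence.

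**2. Does adequacy fill the gap?**

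Inputs (section 2.7), as carbohydrate/fat/protein in % of energy:
- Intervention: 50/35/15
- Control: 55/30/15
- Window: 0.90 to 1.10 times the target

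The comparison assumes the same prescribed calories in both arms and an intake that meets them.

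| Component | Intervention window | Control window | Overlap |
|---|---|---|---|
| Carbohydrate | 45.0 to 55.0 | 49.5 to 60.5 | 49.5 to 55.0 |
| Fat | 31.5 to 38.5 | 27.0 to 33.0 | 31.5 to 33.0 |
| Protein | 13.5 to 16.5 | 13.5 to 16.5 | 13.5 to 16.5 |

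*A control patient exactly on plan (55/30/15).* Against the control diet, adequacy is 100% on all three components. Against the intervention diet it is 55/50 = 110% for carbohydrate (at the edge of the window), 30/35 = 85.7% for fat (outside) and 100% for protein. So adequacy credits this patient for the right diet, and fat separates the two diets.

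*An intake between the two plans (52.5/32.5/15).*
- Against the intervention diet: 52.5/50 = 105%, 32.5/35 = 92.9%, 15/15 = 100%.
- Against the control diet: 52.5/55 = 95.5%, 32.5/30 = 108.3%, 15/15 = 100%.

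Every component lies within 90 to 110% for both diets. The same patient is adequate whichever arm they are in, and whether or not they eat avocado.

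**3. What neither measure is shown to register.** The designed difference in monounsaturated fat is 22% against 12 to 14% of energy, a gap of 8 to 10 percentage points. The gap in total fat is 35 − 30 = 5 points. Adequacy as described counts total fat only, so the larger contrast is not scored. Avocado is not a component either. Section 2.12 pays for avocado in one arm and whole grain bread in the other in order to raise adherence, yet neither food appears in the adherence outcome.

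**4. Baseline.** MEDAS is collected at baseline and 90 days, but section 2.8.2 names only the end value. Minimization balances two categories, below 7 and 7 or above. That protects the comparison between arms at that level. It does not show whether a patient's final score reflects the trial or prior habit.

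**The case against.** The strongest reply is that the same sentence of section 2.8.2 names a second measure that is arm-specific, and this is the only adherence measure for which the article names a model. Control-diet adherence is therefore measured. This stands, and it limits the point: the defect is in MEDAS as a measure for the control arm and in what adequacy leaves out. A measure for that arm does exist.

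A reader might infer that adherent control patients will be classed as non-adherent. The article does not support this. It gives no follow-up MEDAS cut-off; the value 7 is used for previous diet in the minimization, and the outcome is a group median. The control diet also contains whole grains, fruit, vegetables, legumes and daily oil, so an adherent control patient need not score low, and a high score does not by itself prove drift.

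A reader might also infer that compliant control patients will be dropped from the per-protocol set. Section 2.17 does not name MEDAS for that analysis or for the adherence sensitivity analysis, and such definitions are commonly left to an analysis plan. The harm is conditional on MEDAS being chosen.

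Nor are baseline differences ignored: MEDAS is measured at entry and balanced at 7. The fair statement is that the outcome is not described as baseline-adjusted.

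Finally, the MEDAS items are not listed, so the absence of an avocado item cannot be confirmed. It is inferred from the Introduction. A Mediterranean score is also relevant to an avocado-based Mediterranean diet, and comparing it between arms is a legitimate measure of separation. The problem is calling it adherence in both arms.

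**Conclusion.** The point holds in a limited form. MEDAS, as listed, cannot show adherence to the control diet. Percentage of adequacy can, but only for energy and total macronutrients, and its windows overlap enough that one intake satisfies both diets on every component. Neither measure is shown to capture avocado.

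The overlap is partial: fat is the narrowest, with 1.5 percentage points of energy shared, and patients exactly on plan are told apart. How many patients would fall in the shared zone cannot be derived from the article.

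The conclusion rests on equal prescribed calories when the windows are compared, and on the article's own description of MEDAS and of avocado. It affects the adherence outcome and, only if MEDAS were chosen to define adherence, the supporting LDL-C analyses. The primary intention-to-treat analysis does not depend on it. The change is worth making because the needed data are already scheduled.

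**What to change.** 1. In section 2.8.2, relabel MEDAS as a measure of separation between the diets. Report the between-arm difference in 90-day MEDAS adjusted for the baseline score, and do not present it as adherence in the control arm.
2. Keep percentage of adequacy as the arm-specific measure of energy and macronutrient intake.
3. Add intake of the target food in each arm: avocado in the intervention arm and whole grains in the control arm. Take it from the food frequency questionnaire (baseline and 90 days) and the 24-hour recalls (30, 60 and 90 days) in Table 1.
4. State which measure defines adherence in the sensitivity and per-protocol analyses, and do not use MEDAS for control patients there.

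The cost is revised outcome and analysis wording and the extraction of food-item portions from questionnaires already scheduled. No new visit or instrument is needed, and neither diet changes.
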